The proposed intervention is replicable on a national scale and could serve as a model for the future.

The method chosen for data collection, based on collaboration with health insurance departments and extraction of data from the SNDS, will help to limit missing data.

1. **DESCRIPTION OF EXPECTED BENEFITS**

The aim of the study is to identify the most effective ways of reducing the volume of antibiotics dispensed, with immediate benefits for public health:

. limiting the development of bacterial resistance,

. optimising antibiotic prescriptions (better quality prescriptions),

. lower costs.

The results will provide original information, at the end of a randomised comparative study, on the specific impact of 2 complementary types of intervention:

1. the use of visits by health insurance delegates,

2. demonstration of the use of the Antibioclic site.

Secondary analyses will enable us to better characterise the differentiated impact of the intervention according to prescribers or patient characteristics.

The study will provide an opportunity to raise GPs' awareness of the problem of antibiotic resistance on a large scale, and will raise awareness of :

. more than 800 doctors included in arm 1, who will receive awareness training from the Health Insurance delegate, feedback on their practices, and a demonstration of how to use the Antibioclic website,

. more than 800 doctors included in arm 2, who will benefit from awareness-raising by the Health Insurance Delegate and feedback on their practices.

The medico-economic study will document the potential impact on healthcare expenditure.

One of the ancillary benefits of the study will be to mobilise the partners around a joint project, on a theme that is of daily interest to primary care professionals.

1. **OBJECTIVES AND ASSESSMENT CRITERIA**
   1. ***OBJECTIVE AND MAIN EVALUATION CRITERIA***

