. Details of the resources consumed in each arm (averages and dispersion) and the average costs and efficiency per doctor will be calculated for each arm.

. A table will show the difference between the two groups in terms of costs and effectiveness, and the cost-effectiveness ratio will be calculated.

. As costs are not generally distributed according to a normal distribution, the incremental cost-effectiveness ratio and its confidence interval will be estimated using the non-parametric bootstrap method [49].

Finally, the probability that the use of antibioclic associated with a specific DAM visit is cost-effective compared with *a standard DAM visit* will be calculated for different values of willingness to pay for a reduction in antibiotics.

- - 1. ***STATISTICAL JUSTIFICATION FOR THE NUMBER OF INCLUSIONS***

After preliminary work to explore feasibility with the Assurance Maladie teams, the number of eligible doctors was estimated at 2,400 GPs who saw more than 100 different patients in 2018. The average number of DDDs dispensed per doctor in 2018 was 7,671, with a standard deviation of 5,360. In 2018, the average number of DDDs dispensed per doctor was 7671, with a standard deviation of 5360. Due to cluster randomisation, an inflation factor must be applied to calculate the number of subjects. In a previous study in the Loire Atlantique and Vendée regions [47], the average number of GPs per practice was 1.9. We set an intra-class correlation coefficient of 0.05 [50].

With an alpha risk of 5% and power of 80%, we can then demonstrate a significant difference if we have at least an average difference of 450 DDD per doctor (over the 12 months following the DAM visit) between the arms being compared.

- 1. ***Expected degree of statistical significance***

The alpha risk is set at 5%.

- 1. ***Method for taking into account missing, unused or invalid data***

All analyses will be performed on an intention-to-treat (ITT) basis.

The volumes of systemic antibiotics dispensed attributed to doctors who ceased their activity (end of career, moving outside the region, death, etc.) during the study follow-up period will be replaced by multiple imputation. A sensitivity analysis of the per-protocol population will also be carried out, excluding these doctors, as well as those who did not receive a visit from the DAM, and those who were not computerised.

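### The protocol's detectable difference of 450 DDD at 80% power does not follow from its own inputs: it is about 770 DDD, and power at 450 DDD is about 38%

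*Protocol*

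**What the plan says.** The subsection that justifies the number of inclusions (Protocol, Data management and statistics) gives the inputs and a single conclusion.

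- Size: "the number of eligible doctors was estimated at 2,400 GPs who saw more than 100 different patients in 2018".
- Outcome: "The average number of DDDs dispensed per doctor in 2018 was 7,671, with a standard deviation of 5,360".
- Clustering: a mean of 1.9 GPs per practice and an intra-class correlation of 0.05.
- Conclusion, at 5% alpha and 80% power: "we can then demonstrate a significant difference if we have at least an average difference of 450 DDD per doctor". The difference is over 12 months and is described as one "between the arms being compared", so it is a claim about a pair of arms.

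The Randomisation subsection allocates practices 1:1:1. Section 3 (Description of expected benefits) expects "more than 800 doctors included in arm 1" and the same in arm 2. The primary endpoint is compared by an unadjusted Student's t test. Testing is in fixed order: arm 1 against arm 3, then arm 1 against arm 2 only if the first test is significant. Prescribing in the 12 months before the visit is extracted for description only.

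**The concern.** A difference of 450 DDD is only 0.084 of the SD (450 / 5,360). That is small for about 800 doctors per arm in a comparison that removes none of the variation between doctors. All the quantities needed are printed except whether the test is one- or two-sided, so the claim can be checked directly.

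This is the protocol's only power statement, and readers will judge a null result against it. If it is wrong, a non-significant comparison could be taken as evidence against effects of 450 DDD that the trial would usually miss. The fixed testing order adds to the problem. Low power for arm 1 against arm 3 also makes it less likely that arm 1 is tested against arm 2 at all, and that second test carries the question of what the Antibioclic demonstration adds.

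**Working it through.** **Inputs (Protocol).** Total 2,400 doctors, SD 5,360, mean 7,671, mean practice size m = 1.9, ICC = 0.05, alpha 5%, power 80% (sample-size subsection); 1:1:1 allocation (Randomisation), hence 2,400 / 3 = 800 per arm; unadjusted t test (Primary endpoint). The fixed testing order keeps the full 5% at each step, so there is no alpha penalty. Two-sided testing is my assumption; one-sided results are shown as well.

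**Design effect.** DE = 1 + (m − 1) × ICC = 1 + 0.9 × 0.05 = 1.045.

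**Standard error of a pairwise difference.** SE = 5,360 × √(2 × 1.045 / 800) = 274.0 DDD.

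**Detectable difference at 80% power.** (1.960 + 0.842) × 274.0 ≈ 767.5 DDD, and 767.5 / 7,671 = 10.0%. The stated figure is 450 / 7,671 = 5.9%.

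**Power at 450 DDD.** Φ(450 / 274.0 − 1.960) ≈ 0.375. A noncentral-t calculation also gives 37.5%.

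**Doctors needed for 450 DDD.** 2 × 1.045 × (2.802 × 5,360 / 450)² ≈ 2,330 per arm, or about 7,000 in three arms.

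**Attempts to reproduce 450.**

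| Reading | Detectable at 80% power | Power at 450 DDD |
|---|---|---|
| 800 per arm, two-sided, DE 1.045 | 767.5 | 37.5% |
| 800 per arm, two-sided, no DE | 750.8 | 38.9% |
| 800 per arm, one-sided, DE 1.045 | 681.2 | 49.9% |
| 800 per arm, one-sided, no DE | 666.4 | 51.4% |
| Arms 1+2 (1,600) v arm 3 (800), two-sided, DE | 664.7 | 47.5% |
| Arms 1+2 (1,600) v arm 3 (800), one-sided, DE | 589.9 | 59.9% |
| 2,400 split over two arms, two-sided, DE | 626.7 | 52.1% |
| 2,400 split over two arms, one-sided, DE | 556.2 | 64.3% |
| 2,400 in **each** arm, two-sided, DE | 443.1 | 81.2% |

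Only the last row comes near 450 DDD with 80% power, which suggests that the total was used as the per-arm size. Another route also lands close: with 800 per arm, the one-sided critical value is 1.645 × 274.0 ≈ 451 DDD. That is the observed difference at which a one-sided test just reaches significance. It corresponds to 50% power, so it does not support the stated 80%.

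**Could adjustment explain it?** With 800 per arm, 450 DDD requires a residual SD of 5,360 × 450 / 767.5 ≈ 3,143. That means a correlation between pre-visit and follow-up volume of √(1 − (450 / 767.5)²) ≈ 0.81, if the design effect stays at 1.045. The protocol assumes neither.

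**Unequal practice sizes.** The protocol gives no coefficient of variation. If it lies between 0.5 and 1.0 (my assumption), the detectable difference is 776 to 802 DDD.

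**The case against.** The strongest objection is about consequence. The trial takes every eligible GP in the region, so 450 DDD did not set the sample size. The protocol does not call 450 DDD a minimal important difference or an expected effect. Correcting it changes no enrolment, allocation, endpoint or test, and type I error is untouched. All of this is true, and it limits the harm to interpretation. It does not make the sentence correct.

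Three points about precision also stand. The protocol does not say whether the test is two-sided, so the two-sided result is conditional. The figure of 800 per arm is a floor, since the protocol speaks of more than 800; but 900 per arm still gives 5,360 × √(2 × 1.045 / 900) × 2.802 ≈ 724 DDD and about 41% power at 450. The cause of the error cannot be established from the document, and the conclusion does not depend on it.

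One could also argue that adjusting for earlier prescribing would bring 450 DDD within reach. As written, the primary test is unadjusted and the pre-visit data are descriptive. ANCOVA appears only for the secondary question of which physician characteristics go with prescribing. An analysis plan could change the method, but the protocol's figure is stated for the design described there.

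It might be said that arm 1 against arm 2 suffers more because its true difference should be smaller. The protocol gives no expected effect for either comparison, and with equal arms the detectable difference is the same for both, so I do not rely on that.

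**Conclusion.** The stated figure is wrong. On the protocol's own inputs the design has 80% power for about 770 DDD per doctor (10% of the mean), not 450 (5.9%), and about 38% power at 450 DDD. The detectable difference is understated by a factor of about 1.7 (767.5 / 450), and the doctors needed for 450 DDD are about 2.9 times those available (2,330 / 800).

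This rests on two-sided testing, 800 doctors per arm, equal practice sizes and an unadjusted comparison. One-sided testing gives 681 DDD and 50% power. Somewhat larger arms narrow the gap only slightly, and unequal practice sizes widen it.

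**What to change.** Rewrite the concluding sentence of the sample-size subsection. It should say that about 800 doctors per arm, SD 5,360, a design effect of 1.045, two-sided 5% alpha and an unadjusted comparison give 80% power for a difference of about 770 DDD per doctor (10% of the 2018 mean), and about 38% power for 450 DDD. State explicitly whether the test is two-sided; if it is to be one-sided, the figures are about 681 DDD and 50%.

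If the sponsor wants 450 DDD to be within reach, the option that needs no more doctors is to adjust the primary analysis for the volume dispensed in the 12 months before the visit, which is already being extracted. The detectable difference must then be restated with a justified correlation. At the same design effect, 450 DDD is reached only from about 0.81 upwards. The health insurance fund could estimate the correlation from two past years of its own data.

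The basic correction costs one paragraph and a less favourable headline figure. Adjustment would also mean amending the primary analysis and estimating one correlation.

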
- 1. ***Inclusion criteria***

GPs practising in one of the 5 study departments who had seen at least 100 different patients (of any age) in the year preceding the evaluation.

- 1. ***Non-inclusion criteria***

Not included:

. doctors with special practices (acupuncture, allergology, angiology). These doctors will be identified on the basis of health insurance data.

. doctors included in another programme to improve antibiotic prescribing practices run by the Assurance Maladie in the form of a "Plan Personnalisé d'Accompagnement" (CPAM initiative).

. doctors who participated in the design of the study: doctors who took part in the steering groups and working groups, doctors who tested the content of the DAM visit.

1. **DESIGN AND CONDUCT OF THE STUDY**
   1. ***General research methodology***

. This will be a prospective, randomised, controlled, open-label study with 3 parallel arms.

. The study will involve all GPs in the 5 departments of the Pays de la Loire region who meet the inclusion and non-inclusion criteria.

. The statistical unit will be the doctor.

. The source of the data will be the Health Insurance SNDS database for the Pays de la Loire region.

. Randomisation will be based on doctors' surgeries (and not doctors) to limit confounding bias between arms.

. The analysis will be carried out on an intention-to-treat basis.

This is a 'real-life' study.

In particular, it will not be a question of evaluating the effectiveness of the Antibioclic site "*per* protocol".

The challenge will be to assess the effect of the 2 interventions, compared with usual practice, bearing in mind that the Health Insurance Representatives' visit and its potential impact will vary greatly from one doctor to another.

- 1. ***RANDOMISATION; INTERVENTION ARMS and CONTROL ARMS***

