The presentation will describe the practical solutions proposed in response to these 3 causes of overconsumption: presentation of antibioclic (arm 1) or distribution of memo cards (arm 2), discussion of preconceived ideas about antibiotics, and presentation of strategies to help avoid prescribing resulting from the PAAIR study [25].

- the presentation of detailed arguments, so that the DAMs are at ease with the subject, are aware of the specific problems of antibiotic prescribing in primary care, and can answer any questions from the doctors visited.
- presentation of CNAM memo sheets on upper respiratory infections and urinary tract infections. (
  1. ***Inclusions and follow-up period***

The period during which the doctor's prescriptions will be monitored will begin on the date of the DAM's visit (T0). For doctors in arms 1 and 2, the DAM's visit will be staggered over approximately 3 months, corresponding to the time usually required for DAMs to visit all the doctors in their intervention zone. For doctors in arm 3, the date of the DAM's visit will be noted even though the DAM will not be making a specific intervention relating to the prescription of antibiotics (presentation of a different topic during the visit by the Health Insurance Representative to the doctor). Monitoring will last 12 months from the date of the DAM's visit.

- 1. ***Study timetable***

M - 3: Health Insurance Representatives will be trained 3 months before the start of the first visits to doctors.

**T0:** Start of DAM visits to GPs.

M3: End of the cycle of visits made by the DAMs to GPs as part of the study.

Monitoring period*:* The doctor's prescriptions will be monitored from the date of the DAM's visit to the GP (T0). However, the DAMs' visits will be staggered over approximately 3 months, corresponding to the time usually required for the DAMs to visit all the doctors in their area of intervention. For doctors in arm 3, the date of the DAM's visit will be noted even though the DAM will not be making a specific intervention relating to the prescription of antibiotics (presentation of a different topic during the visit by the Health Insurance Representative to the doctor).

*NB: we are anticipating a potential additional 15-day period, beyond the 3-month period initially planned, in order to anticipate some postponements of appointments when doctors are on holiday.*

Monitoring will last 12 months from the date of the DAM's visit.

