**Initial collection**

The Assurance Maladie will be responsible for extracting the data specific to the research and for building up the database.

The data collected will be data characterising GPs: age group (in 5-year increments from the age of 25), sex, classification of the commune of practice (according to INSEE urban area zoning, "major centres" (codes 111, 112, 120), "small centres" (codes 211, 212, 221, 222), "isolated towns" (code 400), and "other communes" (code 300) [46]), activity in terms of number of annual consultations, number of patients in the GP patient base, mode of practice (alone, in a group).

The Assurance Maladie randomises the GPs' places of practice and adds the allocated randomisation arm to the list of participating GPs, according to their place of practice.

The Assurance Maladie extracts data on antibiotic therapy prescriptions from all GPs included in the study (data for the 12 months preceding the visit) for descriptive purposes (T0).

**A 2nd round of** data **collection** will take place at the end of 12 months' follow-up: the French National Health Insurance will extract data on the dispensing of antibiotics prescribed by all GPs included in the study.

The data collection period will begin on the day of the DAM's visit.

- - 1. ***PARTICIPANT IDENTIFICATION***

The data will be centralised by the Assurance Maladie. No nominative data will be exported outside the databases of the Sickness Insurance departments.

The variables were selected after a pilot study, and the health insurance authorities paid close attention to CNIL regulations, to ensure that no data was directly identifiable (which is why the ages of practitioners are grouped into 5-year classes, and the communes classified by type).

- 1. ***Statistics***
     1. ***DESCRIPTION OF PLANNED STATISTICAL METHODS, INCLUDING TIMETABLE FOR INTERIM ANALYSES***

The analyses will be carried out using R 3.6.0 software.

The data will be described by the numbers and percentages of each modality for the qualitative variables and by the minimum, maximum, quartile, mean and standard deviation for the quantitative variables, overall and according to the 3 randomisation arms.

A hierarchical procedure will be used to successively test the comparison between the 3 arms, while maintaining a 5% alpha risk. The first hypothesis tested will be the difference between arm 1 and arm 3. If the test is significant, a second test will be performed comparing arm 1 to arm 2.

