For doctors who have not been visited by the DAMs, the start date of the data collection period will be allocated by drawing lots, and staggered over the 3 months (start date based on the visit dates available for the 3 randomisation arms).

- 1. ***Randomisation***

The Assurance Maladie will generate a list of GP practices that meet the inclusion criteria. It will then randomise the GP practices on a 1:1:1 basis. Doctors will be assigned to the randomisation arm to which their practice has been allocated.

1. **SAFETY / UNDESIRABLE EFFECT**

In the regulatory sense and within the meaning of the Jardé Law, this study does not constitute research involving human subjects. In the regulatory sense and within the meaning of the Jardé Law, this protocol does not involve any change in the usual management of patients, so any adverse events or effects observed will be unrelated to the study.

1. **MEDICO-ECONOMIC STUDY**

This section presents the objectives and methodology of the efficiency analysis, based on a cost-effectiveness analysis. The economic evaluation methodology follows the 2011 recommendations of the French National Authority for Health [49].

- 1. ***Objective, perspective and time horizon of the cost-effectiveness analysis***

The study involves a cost-effectiveness analysis comparing the delivery of antibiotics over a 12-month period in current practice, compared with two alternative strategies

i) an intervention carried out by the Délégués d'Assurance Maladie (Health Insurance Representatives) in general practices, combining a regular visit (with awareness-raising on antibiotic resistance, work on preconceived ideas, feedback on practices) and a demonstration of the use of Antibioclic,

1. an intervention carried out in the same way by the Délégués d'Assurance Maladie, but without Antibioclic being demonstrated.

This analysis will be carried out from the point of view of the Assurance Maladie Obligatoire over a 12-month period.

Costs will be estimated on the basis of information retrieved from the SNDS databases extracted by the Assurance Maladie in Pays de la Loire. The resources consumed will be valued at Assurance Maladie prices for drugs.

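### The allocation rule names no balancing on area, practice size or past antibiotic volume, although these are held before allocation and the primary test does not adjust for them

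*Protocol*

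**What the plan says.** The Protocol describes allocation in three places.

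- **Randomisation** (under Data management and statistics): the Assurance Maladie draws up one list of eligible practices, and "It will then randomise the GP practices on a 1:1:1 basis". Doctors take the arm of their practice.
- **Initial collection**: "The Assurance Maladie randomises the GPs' places of practice and adds the allocated randomisation arm to the list of participating GPs".
- **General research methodology**: the unit randomised is the surgery, and the statistical unit is the doctor.

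None of these names a stratification factor, blocking, minimisation or another restriction.

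Information on practices and doctors exists before allocation. Initial collection lists type of commune, solo or group practice, activity and patient base, all held by the body that randomises. The number of eligible GPs per practice follows from the list itself. Past volume was already used for planning: "The average number of DDDs dispensed per doctor in 2018 was 7,671, with a standard deviation of 5,360".

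The primary endpoint is compared between arms with a Student's t test. The preceding 12 months of prescribing are extracted for description only. Arm 1 v arm 3 is tested first, and arm 1 v arm 2 only if the first test is significant.

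**The concern.** Doctors differ widely in how much they prescribe: 5,360 / 7,671 gives a coefficient of variation of 70%. Visits are made by delegates who work by zone, and the Protocol says of the visit that "its potential impact will vary greatly from one doctor to another". Randomising one list 1:1:1 leaves past volume, area and practice size to chance, and the stated analysis does not take up any imbalance afterwards.

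A sizeable chance gap in past volume would add noise to the 12-month difference, to an extent that depends on how stable a doctor's volume is from year to year. Readers would also find it hard to tell a baseline difference from an effect of the visit. The allocation rule has to be settled before allocation, and here the data needed to improve it are already in hand.

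**Working it through.** **Inputs, all from the sample-size section unless noted**

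- Doctors: "the number of eligible doctors was estimated at 2,400 GPs who saw more than 100 different patients in 2018", so 2,400 / 3 = 800 per arm.
- SD of yearly DDD per doctor: 5,360. Target difference: 450 DDD. Alpha 5% (taken as two-sided), power 80%.
- 1.9 GPs per practice; intra-class correlation (ICC) 0.05.
- Assumption: the 2018 SD and this ICC also describe volume in the baseline year.

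**Step 1. The Protocol's own figure.** It states that a difference is detectable "if we have at least an average difference of 450 DDD per doctor".

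- Design effect = 1 + (1.9 − 1) × 0.05 = 1.045.
- SE of a two-arm difference = 5,360 × √(2 × 1.045 / 800) = 274 DDD.
- Detectable difference = 274 × (1.960 + 0.842) = 768 DDD, not 450. Power at 450 DDD is 38%.

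So 450 DDD is not reproduced. That is a separate problem, but it affects how Step 2 should be read.

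**Step 2. Size of a chance baseline gap.** Under unrestricted allocation the gap in past volume between two arms has the same SD, 274 DDD, which is 274 / 450 = 61% of the target.

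- One comparison (arm 1 v arm 3), either direction: P(|Z| > 450 / 274) = P(|Z| > 1.64) = 10.0%.
- At least one of arm 1 v 3 and arm 1 v 2 (correlation 0.5, because arm 1 is shared): 17.6%; without the design effect, 16.4%. That is about 1 in 6.
- With an ICC of 0.10 to 0.20 and equal practice sizes, the second figure becomes 19% to 21%.

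**Step 3. What restricted allocation would do.** Simulation with 2,400 / 1.9 = 1,263 practices, lognormal volumes, ICC 0.05, five departments and three practice-size classes, in blocks of three ordered by past volume. The year-to-year correlation is not in the Protocol; 0.8 on the log scale is assumed.

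| Quantity (DDD) | Plain 1:1:1 | Stratified, ordered blocks |
|---|---|---|
| SD of baseline gap | about 278 | about 111 |
| SD of 12-month difference, unadjusted | about 280 | about 190 |
| SD of 12-month difference, adjusted for past volume | about 176 | about 173 |

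In a similar simulation, assumed correlations of 0.9, 0.8 and 0.7 gave an unadjusted SD of 158, 187 and 206 DDD under restricted allocation, against about 274 under plain allocation.

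**Step 4. What the model must contain.** If allocation is ordered by past volume but the model holds only department and practice size, the estimated SE stays near 270 while the true SD is about 189.

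- Type I error falls to about 0.7%.
- Power at 450 DDD falls from 38% to about 32%. As a rough check, (1.96 × 270 − 450) / 189 = 0.42, which leaves about 34%.

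With past volume in the model the SE is close to the true SD. At 176 DDD, power at 450 is about Φ(450 / 176 − 1.96) = Φ(0.60) = 73%, on the assumed correlation.

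**The case against.** Four objections carry weight.

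1. **Nothing is invalid.** Unrestricted 1:1:1 allocation of about 1,263 practices is a proper design. The Protocol is silent on balancing; it does not declare the randomisation unstratified, and a separate randomisation plan may add detail. This stands, and it makes the point an improvement rather than an error.

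2. **A chance gap is not bias.** The 274 DDD is simply the standard error of the planned test, and the 5% error rate already allows for it. A reader might infer from the 1-in-6 figure that the trial is likely to give a false result. The documents do not support that.

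3. **The probabilities are large mainly because 450 DDD is not detectable with 800 per arm.** In a trial truly powered at 80% for 450 DDD, the SE would be 450 / 2.80 = 161 and the chance of such a gap 0.5% per comparison. The larger figure also counts both directions and both comparisons, although the second test depends on the first. For arm 1 v arm 3 the chance is 10%, or 5% in the direction unfavourable to arm 1.

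4. **Adjustment for past volume recovers most of the precision without restricted allocation** (176 against 173 DDD). A reader might infer that an imbalance cannot be repaired once practices are allocated. For volume that is wrong, because the prior data are to be extracted anyway. It is equally unsupported that a baseline gap passes almost one for one into the result, since no year-to-year correlation is given.

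What survives is narrower. The stated analysis makes no such adjustment, and balance of area and practice size across arms is worth having when it costs so little.

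**Conclusion.** The point holds as an optional, near-free improvement. The stated rule balances nothing that is known beforehand, and the stated test does not adjust for it. The chance baseline gap has an SD of about 274 DDD. It exceeds 450 DDD with probability 10% for arm 1 v arm 3, and about 17% (16.4% to 17.6%) for at least one comparison. The consequence is lost precision and harder interpretation, not bias or an inflated error rate.

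The gap figures rest on the Protocol's own SD, ICC and practice size, applied to the baseline year. The simulated gains in the 12-month difference also rest on an assumed correlation of 0.8. Most of the precision gain comes from past volume in the model; restricted allocation contributes balance.

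A reader might also infer that particular delegates would deliver one arm disproportionately. The Protocol describes the visiting period as "the time usually required for DAMs to visit all the doctors in their intervention zone", but gives neither the number of delegates nor how the three visit types are shared among them. That effect cannot be sized.

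**What to change.** Before allocation, replace the 1:1:1 sentence in the Randomisation section with:

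> *Practices are randomised 1:1:1 in permuted blocks within strata of department and number of eligible GPs (1, 2, 3 or more), ordered within stratum by mean DDD per doctor in the last complete calendar year. The primary model is clustered by practice and includes the strata and each doctor's prior-year DDD volume.*

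Both sentences are needed: as Step 4 shows, ordering by past volume without the covariate makes the test conservative and does not improve power. The last complete calendar year is used because the 12-month window in Initial collection ends at the visit and is therefore not complete at allocation.

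**Cost:** a few lines in the randomisation program, extra model terms and no new data. The stratum variables and past volumes must be frozen before allocation. Very fine strata, such as delegate zone by practice size, would leave few practices in each and weaken the balance on volume, so department is the safer level.
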